## Background

In comatose patients resuscitated from out-of-hospital cardiac arrest (OHCA), anoxic brain injuries remain the leading cause of death [1]. The overall mortality, though improved considerably over the last decade, continues to be significant and in most countries is as high as 90% [2, 3]. Despite successful resuscitation and admission to an intensive care unit (ICU), the in-hospital mortality is reported to be 30–50% [4, 5]. Functional favorable outcomes among OHCA survivors remain low, and global anoxic brain injury represents a major mechanism of long-term disability [6, 7]. During the post-resuscitative phase, the most significant clinical challenge is to limit secondary brain injury. Targeted temperature management (TTM) targeting 33–36 °C may mitigate cerebral ischemia–reperfusion injury and is recommended in current international guidelines [8–10]. However, managing post-cardiac arrest patients is far more complex than TTM alone, and brain-directed therapies include maintenance of normal oxygenation, ventilation, hemodynamic support to optimize cerebral perfusion, and glycemic control [10, 11].

Reduced cerebral blood flow (CBF), which is mainly dependent upon mean arterial blood pressure (MAP), can result in brain ischemia and enhance secondary brain injury after cardiac arrest. Arterial hypotension may exacerbate brain injury following cardiac arrest because of ongoing cerebral hypoperfusion. Cerebral autoregulation is frequently impaired after cardiac arrest [12, 13], and brain perfusion declines when the MAP falls below 80 to 100 mm Hg. Thus, the generally recommended MAP of above 65 mm Hg [11] to reverse the acute shock state may be inadequate to maintain adequate cerebral perfusion.

When considering blood pressure goals, clinicians should balance the metabolic needs of an ischemic brain with the potential for overstressing a decompensated heart. Post-cardiac arrest myocardial dysfunction, caused by coronary infarction and ischemia–reperfusion injury, is common after CA and resuscitation. Excessive vasopressor use may cause increased afterload and augmented oxygen consumption of the heart, thereby aggravating the myocardial damage [14]. High-dose vasopressor use has been associated with increased mortality [15].

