##### Neuromonitoring during ICU stay

At ICU arrival, patients will be implanted with a jugular bulb MD catheter and monitored for 96 h or until arousal. MD samples are collected in microvials and analyzed every 1 h at the bedside. Regional cerebral oxygen saturation will be monitored by using bifrontal NIRS (Somanetics INVOS Cerebral Oximeter system). Right and left frontal regional oxygen saturation (rSO_2_) values will be recorded simultaneously during ICU stay, and values will be recorded every hour for 96 h or until arousal.

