##### Mechanical ventilation and oxygenation during ICU stay

Patients will be mechanically ventilated, sedated, and when necessary paralyzed with neuromuscular blocking agents to reduce shivering and subsequent heat generation and energy consumption. The study is targeting normal oxygenation (13–14 kPa) during TTM and mechanical ventilation. Ventilation is adjusted, targeting normocapnia of partial pressure of carbon dioxide (paCO_2_) of 4.5–6.0 in all patients.

Serial arterial blood gas will be analyzed open-label by using commercially available equipment adjusted to 37 °C (alpha-stat). The TTM intervention period of 24 h commenced at the time of randomization by using an automated feedback device with temperature control to achieve a target core temperature of 36 °C. After TTM, patients are rewarmed to a core temperature of 37 °C with no more than 0.5 °C per hour. Phase 2 ends when sedation is withheld.

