#### Phase 3 (from end of sedation to 72 h after OHCA)

Sedation is terminated after rewarming when the temperature is at least at 37 °C. Normothermia of 37 °C ± 0.5 °C is maintained until 72 h after the cardiac arrest as long as the patients are managed in the ICU and are unconscious. Nevertheless, weaning from ventilation will be attempted at the earliest possible time during this phase on the basis of typical procedures for discontinuation of mechanical ventilation. Blinded physicians perform a neurological evaluation of patients who remain in coma at 72 h or later after OHCA. The number of patients still comatose at 72 h after the end of TTM who underwent neurological prognostication will be reported. The number of patients who died before neurological prognostication and their presumed cause of death, including limitations in care and explanations for that, will be described. If judged by attending physicians to be indicated, electroencephalogram, somatosensory evoked potentials, and CT of the brain will be performed.

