### Bedside monitoring of cerebral energy microdialysis

Patients will be implanted with a jugular bulb MD catheter (CMA 67 IV 130 mm, MDialysis AB, Stockholm, Sweden) and monitored for 96 h or until arousal. The catheter allows energy-related metabolites to diffuse into the catheter reflecting accurate concentrations in the venous blood, CE marked according to the Medical Device Directive, 93/42/EEC. MD catheters are inserted in a retrograde direction into the jugular bulb, through a peripheral intravenous 17 GA cannula by using ultrasound guidance, as performed in a previous study [29]. The positioning of the catheter tip in the jugular bulb above the inlet of the common facial vein is confirmed on cranial CT scan in accordance with earlier practice [33]. MD pumps (CMA 106, MDialysis AB) at 0.3 μL/min perfuse MD catheters. The perfusates are collected in microvials, analyzed every 1 h for minimum 96 h by enzymatic photometric techniques, and presented at the bedside (Iscus, Mdialysis AB). The analyses include the biochemical variables regularly monitored during intracerebral MD: glucose, pyruvate, lactate, glutamate, and glycerol. Clinical data, radiology, electroencephalography, somatosensory evoked potential, and NIRS will be recorded.

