### Statistical analysis plan

The statistical analyses will be the following:Analyses will be performed in accordance with the intention-to-treat principle and will take into account patients lost to follow-up.A two-sided significance level of 0.05 will be applied to both primary and secondary end-points.Unpaired *t* tests or Mann–Whitney *U* tests will be conducted for unpaired comparisons of numerical variables. A chi-squared or Fisher’s exact test will be conducted to examine differences between categorical variables.Association between LP ratio and “poor” neurological outcome (CPC 3–4) will be assessed with chi-squared test and logistic regression. The overall expected rates of unfavorable neurological outcome (CPC 3–4) are 5–7%, observed in earlier studies [34, 35]. The multivariate logistic model will be adjusted for time to ROSC, arterial carbon dioxide partial pressure, baseline LP, and average LP ratio > 30 > 24 and 48 h as covariates.Association between LP ratio and all-cause mortality will be assessed with chi-squared test and logistic regression.Receiver operating characteristic (ROC) curves will be constructed to determine the sensitivity and specificity of the LP ratio levels at each time point (and the maximal LP ratio level recorded during the ICU period) for predicting outcomes.Association between total duration (in minutes) of cerebral desaturation (rSO_2_ ≤ 50%) and unfavorable neurological outcome (CPC 3–4) and death will be assessed with chi-squared test and logistic regression.Time from start of randomization to death in the two blood pressure groups will be assessed by using the Kaplan–Meier method, and group differences will be tested by log-rank test. Cox regression will be applied for adjusted comparisons and estimation of hazard ratios.In regard to dynamic changes of MD variables in the two blood pressure groups, longitudinal models, applying linear mixed effects regression, will be used to account for repeated measurements of MD biomarkers across different patients over time.In regard to dynamic changes of blood pressure, longitudinal models, applying linear mixed effects regression, will be used to account for repeated measurements of blood pressure across different patients over time.

All standard assumptions regarding statistical models will be checked. Statistical analysis will be performed by using STATA V.15 (StataCorp LLC).

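### The maximal LP ratio over the ICU period is taken over a window whose length depends on the outcome, so its ROC curve can depart from 0.50 with no prognostic signal

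*Protocol article*

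**What the plan says.** The ROC item in the Statistical analysis plan section uses two kinds of predictor: the LP ratio at each time point, "and the maximal LP ratio level recorded during the ICU period) for predicting outcomes". The second has no window other than the ICU period.

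Sampling is hourly: "MD samples are collected in microvials and analyzed every 1 h at the bedside". Under Neuromonitoring during ICU stay, patients are "implanted with a jugular bulb MD catheter and monitored for 96 h or until arousal". The section Bedside monitoring of cerebral energy microdialysis repeats that stopping rule, but also says the perfusates are "analyzed every 1 h for minimum 96 h by enzymatic photometric techniques". The two statements conflict for any patient who wakes before 96 h.

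Two further statements fix when waking becomes likely. "The TTM intervention period of 24 h commenced at the time of randomization", and "Sedation is terminated after rewarming when the temperature is at least" 37 °C.

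Fixed-window LP summaries exist elsewhere in the article: the 48 h mean for the primary end-point, and LP above 30 averaged over 24 and 48 h. The latter is also a covariate in the neurological outcome model. The item on LP and mortality names no LP summary.

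**The concern.** Waking is both a stopping rule for sampling and close to the opposite of the poor outcome, since CPC 4 is defined as coma. An early waker contributes roughly a day or more of hourly values, a persistently comatose patient about 96, and an early death only a few. The expected maximum of a varying series rises with the number of values, so the predictor partly records how long the patient was observed.

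Prognosis is a declared purpose of the trial: the aims include the correlation of LP with neurological outcome, and the Discussion claims implications for early prognosis. An AUC for the whole-stay maximum could be read as evidence that LP predicts outcome when some of it reflects monitoring length. Nor could it be applied at the bedside at a known hour, because the maximum is known only once monitoring has ended.

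**Working it through.** The plan gives no figure for this analysis, so there is none to reproduce. The between-patient SD of 15 is borrowed from the Sample size estimation section. That section's total of 46 is reproduced by a two-sample t-test (difference 15, SD 15, two-sided 0.05, power 0.90: 23 per arm).

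**1. Number of values per patient**
- Earliest end of sedation: 24 h of TTM plus rewarming from 36 to 37 °C at no more than 0.5 °C per hour, so 24 + (37 − 36)/0.5 = 26 h after randomization. Arousal comes at or after this point; the documents do not give its timing.
- Persistent coma: up to about 96 hourly values.
- Early death: as few as a handful.

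**2. Model with no prognostic information**
LP for patient i at hour t = common mean + b_i + w_it, with b_i normal (between-patient SD) and w_it a first-order autoregressive series (within-patient SD, lag-1 correlation 0 to 0.95). The distribution is the same whatever the outcome, so the true AUC is 0.50. The AUC is the probability that the maximum of a patient with 96 values exceeds that of a patient with 30. The figure of 30 is an assumption, set a little after the 26 h point. Within-patient SD, correlation and between-patient SDs other than 15 are also assumptions. The early-peak columns add an excess of 15 or 30 LP units that decays with a 12 h time constant, again assumed.

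| Between / within SD | AUC, stationary | AUC, early excess 15 | AUC, early excess 30 |
|---|---|---|---|
| 15 / 5 | 0.54–0.56 | 0.50–0.51 | 0.50 |
| 15 / 10 | 0.58–0.61 | 0.51–0.54 | 0.50–0.51 |
| 15 / 15 | 0.62–0.65 | 0.56–0.59 | 0.51–0.53 |
| 10 / 10 | 0.61–0.65 | 0.53–0.56 | 0.50–0.51 |
| 7 / 13 | 0.67–0.70 | 0.57–0.61 | 0.51–0.53 |

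**3. Same window for everyone**
With the maximum taken over the first 24 h in both groups, the AUC returns to 0.50 (simulation range 0.495–0.504). Window length is therefore the cause.

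**4. Death as the outcome, cohorts of 60**
Mortality was set at 30–50% (the in-hospital range in the Background) and correlation at 0.5. Assumed: 0–80% of deaths fall during monitoring, and 50–80% of survivors wake before 72 h.
- Deaths after prolonged coma, 80% of survivors waking early, SD 5/10: AUC 0.59–0.60, with rejection at the nominal 5% level in about 22–25% of trials.
- 80% of deaths during monitoring, 50% of survivors waking early, SD 5/10: AUC 0.42, rejection about 14–19%.
- 50% of deaths during monitoring, 80% waking early: AUC 0.50–0.51; the two effects cancel.
- At SD 15/15 the range over all scenarios is about 0.45–0.56.

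Overall the AUC runs from about 0.42 to 0.60, and rejection from about 4% to 25%.

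**5. LP at a single hour**
Among patients still monitored at 24 h, the AUC with no true association is 0.495–0.506. No drift arises.

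**The case against.** The strongest reply is that this is one predictor, named in a parenthesis of an exploratory ROC item, and that its bias cannot be sized from the documents. That is largely fair. Neither the within-patient SD nor the time course of LP is given, and if LP peaks soon after resuscitation the effect shrinks markedly, in some settings to nothing. The article also expects CPC 3–4 in only 5–7% of patients, which is 3 to about 4 of 60 (0.05 × 60 = 3; 0.07 × 60 = 4.2), so an ROC curve for that outcome will be imprecise whatever the window. And if sampling really ran for at least 96 h in everyone, survivors would have equal windows. But the same section also allows sampling to stop at arousal, so this defence depends on a contradiction that the article leaves open.

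A reader might infer more than the text supports:
- **That the curves at each time point are inflated too.** LP at a given hour does not depend on later follow-up. After about 26 h, however, the patients with a value are a selected and shrinking group.
- **That the mortality association is built in.** This would need a whole-stay summary in that model, and the article does not say that one is used. With 24 h or 48 h averages, earlier deaths have incomplete windows, which is a different and smaller matter.
- **That the bias always favours LP as a predictor.** Prolonged coma raises the maximum and early death lowers it, so for death it can inflate, hide or reverse an association.

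What stands is the maximum itself: the article does state a window for it, and that window has no common length.

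**Conclusion.** The point holds for the maximal LP ratio. As written, its observation window depends on arousal and death, and its AUC can depart from 0.50 with no true association: about 0.54–0.70 for 96 versus 30 values with a stationary series, about 0.50–0.61 with an early peak, and about 0.42–0.60 for death in mixed cohorts. The mechanism follows from the protocol's own stopping rule. The sizes rest on between-patient SD 7–15 (5–15 in the mixed cohorts), within-patient SD 5–15 and assumed timing of waking and death. The single-hour curves have a selection problem after about 26 h rather than a built-in bias. The randomized comparison of mean LP over 48 h is not touched by this point. It deserves correction because the prognostic reading of LP is a stated aim, but it does not threaten the trial's main result.

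**What to change.** 1. Take the maximum (and mean) LP over a common early window, such as the first 24 h from randomization, which ends before the earliest end of sedation at about 26 h. Relate it to later outcome among patients alive and monitored at 24 h, and list earlier deaths separately.
2. Limit ROC curves to a few prespecified early hours and report how many patients have a value at each.
3. Use the same fixed-window summary in the mortality model.
4. Reconcile the two statements on monitoring length in Bedside monitoring of cerebral energy microdialysis, "monitored for 96 h or until arousal" against a minimum of 96 h.
5. Keep ICU mortality as the stated secondary end-point; replacing it would change an end-point in a trial already enrolling. Three-month vital status can be added as a sensitivity analysis. The Phase 5 section obtains it by examination or telephone interview and uses the civil registration system at the end of the trial.

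The cost is analysis wording, with no new data. The downside is that deaths before 24 h leave the landmark analysis, so its conclusions apply only to patients who survive that long.

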### Trial profile

A flowchart of the study participants will be presented in accordance with the Consolidated Standards of Reporting Trials (CONSORT) diagram [36, 37].

### Baseline data

The predefined baseline variables are the following:SexAgeComorbidities (premorbid CPC, ischemic heart disease, heart failure, previous cardiac arrest, arterial hypertension, stroke, epilepsy, diabetes, chronic obstructive pulmonary disease, chronic hemodialysis, and alcoholism)Previous percutaneous coronary interventionPrevious coronary artery bypass graftPrevious valvular surgeryImplantable cardioverter-defibrillator or pacemaker or bothPre-hospital variablesLocation of cardiac arrestBystander-witnessed arrestBystander cardiopulmonary resuscitationShockable primary rhythmTime to basic life supportTime to advanced life supportTime to ROSCAdmission variablesFirst measured temperatureGlasgow Coma Scale scoreShock at admissionPresumed cause of cardiac arrest (cardiac/non-cardiac)Acute myocardial infarctionSerum pHSerum lactateEnd-tidal carbon dioxideBlood pressureResult of angiogramCardiac troponin (TnI) and creatine kinase-muscle/brain (CK-MB).

Differences in baseline variables between blood pressure groups will be analyzed and presented in tables. Continuous variables will be presented as mean ± SD, and differences will be analyzed with the unpaired *t* test. In case of non-normally distributed data, continuous variables will be presented as median (interquartile range) and a *t* test will be applied following logarithmic transformation if the transformed data are normally distributed; alternatively, the non-parametric Mann–Whitney test will be applied. Categorical variables will be presented as counts and percentages and differences will be analyzed with the chi-squared test or Fisher’s exact tests if counts below 10 are observed.

## Discussion

The mortality of patients who are admitted in a comatose state to an ICU following successful resuscitation after cardiac arrest remains significant. The necessity for early and accurate prognostic predictors is important, especially since sedation and TTM might change the neurological examination and postpone the recovery of motor response for several days. Markers measuring global cerebral ischemia caused by cardiac arrest and consecutive resuscitation and reflecting the metabolic variations after successful resuscitation are urgently required to assist more personalized post-resuscitation care and prognostication.

Jugular bulb MD may provide a reliable global estimate of cerebral metabolic state and can be implemented as an entirely new and less invasive diagnostic tool for ICU patients after OHCA and has implications for early prognosis and treatment. The LP ratio assessed from MD of cerebral venous blood may play a critical role in detecting the early responses of post-resuscitation care and may predict in-hospital and long-term prognosis in patients affected by brain injury after cardiac arrest. In the future, this might optimize and individualize the treatment of post-cardiac arrest patients and potentially improve outcome.

## Surrogate end-point

The end-point defined as the LP ratio during ICU stay is a surrogate marker for poor neurological outcome and death. The surrogate marker is used as an alternative to a hard end-point in order to power this study adequately. Previously, LP ratio studies have been shown to be a reliable marker for poor outcome after traumatic brain injury [22–26]. Hence, our surrogate end-point reflects the clinically relevant question of whether higher MAP has a potential neuroprotective effect in our population.

## Strengths and limitations of this study

Jugular bulb MD may provide a reliable global estimate of cerebral metabolic state and can be implemented as an entirely new and less invasive diagnostic tool for ICU patients after OHCA and has implications for early prognosis and treatment.This pragmatic trial is addressing the effect of higher MAP on global cerebral metabolism in patients resuscitated from OHCA.Randomized controlled trial design minimizes the risk of selection bias.Clinicians are not blinded to data obtained at the bedside from jugular bulb MD, so all outcome assessors will be blinded to minimize the risk of bias.Until now, no established gold standard method assessing global cerebral energy state has existed. Therefore, it is not possible to compare jugular bulb MD with an established method already in clinical use.

## Trial status

Protocol version 1.1. Date: March 8, 2018. The study is ongoing and currently enrolling. Recruitment began January 11, 2017, and is expected to be completed around January 8, 2020.

## Abbreviations

CBF: Cerebral blood flow
CPC: Cerebral performance category
CT: Computed tomography
ICU: Intensive care unit
LP ratio: Lactate-to-pyruvate ratio
MAP: Mean arterial blood pressure
MD: Microdialysis
NIRS: Near infrared spectroscopy
OHCA: Out-of-hospital cardiac arrest
PAC: Pulmonary artery catheter
ROSC: Return of spontaneous circulation
rSO_2_: Regional oxygen saturation
SD: Standard deviation
SPIRIT: Standard Protocol Items: Recommendations for Interventional Trials
TTM: Targeted temperature management
